## Abstract

**Background:**

Cardiovascular disease has a multifactorial aetiology with a number of both modifiable and non-modifiable risk factors. Although evidence indicates that dietary intake plays an important role, few studies have focused on the effect of fruit and vegetable consumption on early markers of vascular function. Therefore, we hypothesised that supplementation with capsules containing a combination of fruit and vegetable extracts over 12 weeks can significantly modulate biomarkers of vascular function compared with a control group receiving placebo.

**Methods/Design:**

This is a double-blind, randomised controlled trial that includes overweight and obese but otherwise healthy participants. Participants are randomly allocated to one of two groups: active supplementation (encapsulated fruit and vegetable powder) or placebo taken twice daily for 12 weeks, whereas both groups will be given the ‘5-A-Day’ dietary advice. The primary outcome is to measure changes to the carotid intima media thickness (cIMT) between the two groups from baseline (test visit 1) to 12 weeks later (test visit 2). The secondary outcomes include macro- and microvascular changes and changes to blood markers.

**Discussion:**

In addition to the primary and secondary objectives, this explanatory trial incorporates potential novel biomarkers such as trimethylamine-N-oxide (TMAO) and lipopolysaccharide (LPS).

**Trial registration:**

ISRCTN14315618. Registration date 27 February 2014.

## Background

### Background and rationale

Increasingly, dietary intake and nutrition are recognised as playing a major role in the aetiology of CVD [1]. A number of epidemiologic and observational studies regularly report that consuming fruit and vegetables (F&Vs) can lower CVD risk. Among several studies that have looked into the beneficial effects of F&Vs in lowering CVD risk, Yusuf and colleagues [2] reported that the population attributable risk for acute myocardial infarction given irregular consumption of F&Vs was 12.9 %. Also, Crowe and colleagues [3] reported that participants consuming at least 80 g of F&Vs per day had a 22 % lower risk of fatal ischaemic heart disease. Berry fruits have also been shown a reduction in blood pressure as well as a reduction in the levels of pro-inflammatory markers and adhesion molecules, which are both markers of endothelial function [4].

Endothelial dysfunction is emerging as a potential set of early markers of cardiovascular disease risk. It is considered to play a principal role in the initiation and progression of atherosclerosis, and it is also present in later stages of vascular disease. Many studies have used a variety of tests in order to measure endothelial function as well as to assess the impact of potentially therapeutic interventions on the vasculature [5]. In a placebo-controlled crossover study, a short fruit extract intervention study led to improved endothelial vasodilation measured by flow mediated dilatation (FMD) in individuals at risk for CVD [6].

Evidence suggests that dietary flavonoids work in various ways and reduce oxidative stress, which is caused by factors such as smoking, obesity, hypertension and other pathological conditions [7]. Specifically, phytonutrients in F&Vs may have specific cardio-protective effects partially mediated through favourable effects on endothelial function, inhibition of angiogenesis and cell migration and proliferation in blood vessels [8]. Although recent health and public reports focus on the five portions of a range of F&V as being cardio-protective [9, 10], clear dose-response relations are poorly defined, which has resulted in major inconsistencies in F&Vs recommendations. Overall, the body of evidence is growing on the modulation of endothelial, as well as macro- and microvascular function (predictive of cardiovascular risk), due to interventions using different categories of F&Vs or chronic ingestion of selected phytonutrients. However, a paucity of studies have examined the vascular modulatory effects of chronic unselective exposure to a high dose of a very wide range of phytonutrients derived from F&Vs, and it is currently not known whether this can bring about similar magnitudes and patterns of vascular change as compared with exposure to selected F&Vs. We hypothesize that a high dose of unselective phytonutrients derived from F&Vs, when ingested chronically, will result in potentially beneficial changes (compared with placebo) to both macro- and microvascular measures, through modulation of endothelial and conduit function of arteries, thus mitigating cardiovascular risk.

## Methods/Design

### Aim/Objectives

The aim of this study is to evaluate the effects of supplementation with encapsulated fruit and vegetable powder compared with placebo on vascular and endothelial function before and after 12 weeks of intervention when they are both given with ‘5-A-Day’ dietary advice verbally and in writing.

Specifically, the primary objective of this trial is to assess whether there is a change in the carotid intima media thickness (cIMT) between the two groups.

The secondary objectives are to assess the following:Dynamic macrovascular and microvascular changes.Changes in laboratory blood markers, including endothelial cell function and oxidative stress.Changes in Knowledge, Attitudes and Practices (KAP) using the Five-a-day Community Evaluation Tool (FACET).Changes to safety indicators: liver function, routine bloods (including full blood count) and ECG.

### Study design

This study is a double-blind, randomised controlled trial for overweight and obese but otherwise healthy participants. It is being conducted at the Medical Research Council (MRC), Human Nutrition Research (HNR) unit in Cambridge, United Kingdom. The study had two stages of ethical approval; first, an internal research governance approval was granted by the Research Review Board (RRB) at MRC HNR, which comprises joint scientific and ethical peer review. Full independent research ethics approval was subsequently obtained from the NHS National Research Ethics Service (REC Reference: 13/EE/0095) and fully informed written consent is taken from all participants. Confirmation that this study does not fall under the legal definition of a Clinical Trial of an Investigational Medicinal Product (CTIMP) was sought from the Medicines and Healthcare Products Regulatory Agency (MHRA) Borderline Team.

### Participants and setting

#### Inclusion criteria

Participants are eligible for this study if they fulfil the following criteria: (1) aged between 25 and 65 years; (2) BMI 25 to 35 kg/m^2^; (3) able and willing to take gelatin casing capsule supplements for 12 weeks and complete the required evaluations; and (4) competent and willing to give informed consent.

#### Exclusion criteria

People with any of the following will be excluded from participation: (1) all diagnosed cardiovascular risk factors or disorders; (2) diabetes and disorders of glycaemic control; (3) irritable and inflammatory bowel disorders and acid peptic disease; (4) any active tumours/cancers; (5) lipid or cholesterol lowering tablets; (6) continuous use of any nutritional supplements and/or prescription medication likely to impact on study measurements or safety; (7) pregnancy or breastfeeding; (8) high-dose aspirin and analogues; (9) high levels of physical activity; (10) current active mental and/or neurological illness and the use of related medication; and/or (11) currently smoking.

### Sample size

The sample size calculation was performed according to cIMT changes over 12 weeks of supplementation. cIMT normal values in the general adult population (including overweight individuals) less than 65 years of age, range from 0.60 to 0.80 mm with a SD of 0.10 mm. [7]. Assuming a two-tailed t-test using a 5 % significance level (two-sided), a sample size of 37 in each group (74 participants in total) was determined to have 85 % power to detect a mean cIMT difference of 0.07 mm after 12 weeks of supplementation between the intervention and control groups, assuming a common SD of 0.10 mm. Allowing for a dropout rate of approximately 15 %, we aim to recruit 80 participants in total; *n* = 40 in the placebo and *n* = 40 in the intervention group.

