### Data analysis

A consort flowchart of enrolled participants will be provided, and the demographic characteristics recorded at the time of randomisation will also be described. Descriptive analysis will be conducted for all baseline variables to compare participants in both study groups. Results will be reported as means and standard deviations for continuous variables and frequencies with percentages for categorical variables. Two group comparisons for changes in primary and secondary outcome measures following 12 weeks of intervention will be made, assuming similar levels of variance between the two treatment groups and using two-tailed t-tests for normally distributed data. Paired t-tests will be used to assess within-group changes in study outcomes. Multiple linear regression models will be used to assess whether changes from baseline to 12 weeks were significant between the study groups. Regression analysis will be conducted, with adjustment for potential baseline confounding variables. Additionally, a sensitivity analysis will be performed, exploring variation in the standard deviation between the differences of the mean change in cIMT measurements. Exploratory within-group changes will also be assessed for each outcome measure.

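### The 85 % power is stated for 12-week cIMT change but rests on the SD of single cIMT values, so the power of the planned change analysis is not established

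*Protocol article*

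**What the plan says.** The abstract of the protocol article (Methods/Design) defines the endpoint as a change: "The primary outcome is to measure changes to the carotid intima media thickness (cIMT) between the two groups from baseline" to week 12. The Data analysis section follows this, with a two-group t-test on the 12-week changes and multiple linear regression on change from baseline, adjusted for baseline confounders that are not named.

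The Sample size section also begins with change: "The sample size calculation was performed according to cIMT changes over 12 weeks of supplementation". Its next sentence supplies the SD. Normal cIMT values in adults under 65 are said to "range from 0.60 to 0.80 mm with a SD of 0.10 mm". The calculation then takes that value over, "assuming a common SD of 0.10 mm", and concludes that 37 per group give "85 % power to detect a mean cIMT difference of 0.07 mm after 12 weeks of supplementation between the intervention and control groups".

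The Data analysis section also plans a sensitivity analysis "exploring variation in the standard deviation between the differences of the mean change in cIMT measurements", without giving a value for that SD.

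**The concern.** The SD of single values describes how much people differ from one another at one visit. The SD of change describes how much a person's two readings, 12 weeks apart, differ. The two are linked by the correlation between the readings and are equal only at one value of it. The paragraph therefore claims power for one quantity using the SD of another.

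cIMT is the outcome on which the trial was powered (Discussion). The stated power and the 0.07 mm target are what a reader has for judging what the trial could detect. That target is 10 % of 0.70 mm, the middle of the quoted normal range. If repeat readings are strongly correlated, the change analysis can detect differences well below 0.07 mm. If they are weakly correlated, an unadjusted comparison of changes has less power than stated.

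**Working it through.** **Inputs from the Sample size section.** Difference 0.07 mm; SD 0.10 mm in each group; two-sided 5 % level; 37 per group; 85 % power.

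**Step 1: reproduce the plan's figure.** By the normal approximation, n per group = 2 × (1.960 + 1.036)² × (0.10/0.07)² = 36.6, rounded up to 37. At 37 per group the power is 85.3 % by the normal approximation and 84.4 % by the exact (noncentral) t-test; the exact t-test needs 38 per group for 85 %. The figure reproduces. Because 0.10 mm is the SD of single values, it is the power of a comparison of week-12 values.

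**Step 2: translate to change.** With the same SD at both visits (assumption) and correlation r between them,

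SD of change = 0.10 × √(2(1 − r)).

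Setting this equal to 0.10 gives 2(1 − r) = 1, so r = 0.5. The document does not state or justify that value.

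**Step 3: power of the unadjusted t-test on change, 37 per group.** The document gives no r, so these values are assumptions shown as a range. Power is by the exact t-test for 0.07 mm. The difference detectable with 85 % power is 0.706 × SD of change, where 0.706 is the standardised difference that 37 per group detect with 85 % power.

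| r (assumed) | SD of change (mm) | Power for 0.07 mm | Detectable difference at 85 % power (mm) |
|---|---|---|---|
| 0.3 | 0.118 | 71 % | 0.084 |
| 0.5 | 0.100 | 84 % | 0.071 |
| 0.7 | 0.077 | 97 % | 0.055 |
| 0.8 | 0.063 | above 99 % | 0.045 |

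**Step 4: the same inputs with baseline cIMT as a covariate.** The residual SD is 0.10 × √(1 − r²), which cannot exceed 0.10 mm. At 37 per group:

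| r (assumed) | Residual SD (mm) | Power for 0.07 mm | Detectable difference at 85 % power (mm) |
|---|---|---|---|
| 0 | 0.100 | 84 % | 0.071 |
| 0.3 | 0.095 | 88 % | 0.067 |
| 0.5 | 0.087 | 93 % | 0.061 |
| 0.7 | 0.071 | 99 % | 0.050 |
| 0.8 | 0.060 | above 99 % | 0.042 |

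Under this analysis the plan's SD is an upper bound, and power at 37 per group is at least about 84 % whatever r is.

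**The case against.** **The number is not wrong.** It follows from its inputs, and at r = 0.5 it is also the power for change. This stands: the fault is an input that does not match the endpoint, and the consequence is that the power is unsupported.

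**The target could be a difference in week-12 values.** The phrase about a mean difference after 12 weeks allows that reading. It would make the SD appropriate, but it would conflict with the section's opening sentence and with the tests on change in Data analysis. The paragraph would still need correcting.

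**0.10 mm may be conservative anyway.** For a structural measure repeated after 12 weeks, a high r is plausible, though that is an assumption. With baseline cIMT as a covariate, 0.10 mm is conservative for any r. But the planned t-test on change is unadjusted, and the regression does not name baseline cIMT among its covariates. This objection points to the remedy without rescuing the statement as written.

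**An article condenses a fuller protocol.** That would excuse a missing source or derivation. Here the endpoint, the SD, its origin and the test are all printed, and they do not fit together.

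Two stronger readings are tempting. A reader might infer that the trial is underpowered. The documents give no r, and above r = 0.5 the change analysis has more power than stated. A reader might also take the sensitivity analysis on the SD of change as an admission that the design SD was wrong. Its wording is ambiguous: it does not mention sample size, and it may be a check on the equal-variance assumption made earlier in the same section. It is prespecified, supplies no SD of change, and gives no reason for its own removal.

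**Conclusion.** The concern holds as a mismatch between the planning SD and the endpoint. The stated 85 % is sound for week-12 values. It is not shown to be the power of the planned t-test on change, with which it agrees only at an unstated r = 0.5. Over r = 0.3 to 0.8 that power runs from 71 % to above 99 %, and the detectable difference from 0.084 down to 0.045 mm. These figures assume an SD of 0.10 mm at both visits and 37 analysed per group. The direction of the discrepancy cannot be settled from the document, and the point should not be reported as a loss of power.

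The dropout allowance is a separate matter: 80 × 0.85 = 68, or 34 per group instead of 37. It plays no part in the figures here.

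**What to change.** Keep the recruitment target of 80. Name week-12 cIMT adjusted for baseline cIMT as the primary analysis, and restate the power and detectable difference for it, noting that 0.10 mm is then a conservative SD. If the change-score t-test is to stay primary, give the SD of 12-week change with its source, or show power and detectable difference over a stated range of r. In either case, interpret a null result by its 95 % confidence interval and not by the 0.07 mm planning difference. The planned sensitivity analysis can remain.

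The cost is a rewritten sample-size paragraph and, for the preferred option, one sentence in Data analysis naming the covariate. Baseline cIMT is already measured at test visit 1, so no data collection or enrolment changes.

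### Recruiting 80 does not cover the stated 15 % dropout: 68 completers (34 per group) remain, with about 81 % power on the plan's own inputs rather than 85 %

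*Protocol article*

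**What the plan says.** All the figures stand in the Sample size section of the protocol article.

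- **Test:** "Assuming a two-tailed t-test using a 5 % significance level (two-sided").
- **Effect:** the trial is sized "to detect a mean cIMT difference of 0.07 mm after 12 weeks of supplementation between the intervention and control groups".
- **Variability:** the calculation is made "assuming a common SD of 0.10 mm".
- **Size and power before dropout:** "a sample size of 37 in each group (74 participants in total) was determined to have 85 % power".
- **Dropout and target:** "Allowing for a dropout rate of approximately 15 %, we aim to recruit 80 participants in total", split 40 and 40.

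So 74 is the number needed at analysis, and 80 is offered as the number that protects it against loss. No other section gives a different dropout rate, evaluable number or target. The Discussion confirms that cIMT is the outcome on which the trial was powered.

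**The concern.** An allowance of about 15 % on 74 should add at least 11 participants by any usual method, but the plan adds 6. One of the three figures (85 % power, 15 % dropout, 80 recruited) therefore has to give way.

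This passage is the only power justification for the primary comparison. A reader facing a null result on cIMT would take from it that the trial had 85 % power even after 15 % loss. If that is not so, the chance of missing a true 0.07 mm difference is higher than the article says.

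The loss bears directly on the primary outcome. The schedule of data collection (Table 2) places cIMT only at test visit 1 (week 0) and test visit 2 (week 12). A participant who leaves before week 12 has no observed change in cIMT.

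**Working it through.** **Inputs (Sample size section).** Two-sided alpha 0.05; difference 0.07 mm; SD 0.10 mm, so d = 0.07/0.10 = 0.7; target power 85 %; 37 per group; dropout 15 %; 80 recruited, 1:1.

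**Step 1. Reproduce the plan's 37 per group.** By the normal approximation,

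n per group = 2(1.960 + 1.036)² / 0.7² = 36.6, rounded up to 37.

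The base size reproduces. Power at 37 per group is 85.3 % by the normal approximation and 84.4 % by the noncentral t. The exact t-test calculation asks for 37.6, that is 38 per group, a trivial difference.

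**Step 2. Inflate for dropout.**

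- Standard method, n/(1 − d): 74/0.85 = 87.06. With equal groups, 37/0.85 = 43.5, so 44 per group and 88 in total.
- Common shortcut, n × (1 + d): 74 × 1.15 = 85.1, so 86 with equal groups.

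Neither gives 80.

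**Step 3. The allowance that 80 really gives.** 1 − 74/80 = 6/80 = 7.5 %, half the stated rate.

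**Step 4. Power with 80 recruited and 15 % dropout.** 80 × 0.85 = 68 completers, 34 per group if losses fall equally.

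| Completers per group | Noncentral t | Normal approximation |
|---|---|---|
| 37 (as planned) | 84.4 % | 85.3 % |
| 34 (80 recruited, 15 % lost) | 81.2 % | 82.3 % |
| Loss | 3.2 points | 3.0 points |

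By the t-test, the chance of missing a true 0.07 mm difference is 18.8 % with 34 per group. It is 15.6 % with 37 per group by the same method, and the plan implies 15 %.

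**Step 5. Detectable difference at 85 % power (noncentral t).** 0.0738 mm with 34 per group, against 0.0706 mm with 37 per group and the 0.07 mm stated.

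**Step 6. Can the word *approximately* close the gap?** With 80 recruited, by the noncentral t:

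| Dropout | Completers | Power |
|---|---|---|
| 7.5 % | 74 | 84.4 % |
| 10 % | 72 | 83.4 % |
| 12.5 % | 70 | 82.3 % |
| 15 % | 68 | 81.2 % |
| 17.5 % | 66 | 80.0 % |

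The planned 74 completers are kept only at 7.5 % dropout or less, which is not a rounding of 15 %.

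**The case against.** The arithmetic itself is hard to defend, so the case on the other side concerns its weight and its conditions.

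- **The gap is smaller than 85 to 81.** The plan's 85 % fits the normal approximation, while 81 % comes from the noncentral t. Like for like, the loss is 84.4 to 81.2 %, or 85.3 to 82.3 %. This stands: dropout costs about 3 points, and the rest of the gap is a difference of method. By either method, though, power at 34 per group is below 85 %.
- **The practical effect is small.** Power stays above 80 %, and the detectable difference moves by about 0.003 mm (0.0706 to 0.0738) beside an SD of 0.10 mm. This also stands. It limits the consequence but does not make the statement correct.
- **81 % is not the trial's actual power.** The Data analysis section also plans comparisons of change and regression adjusted for baseline variables. The article gives no correlation between baseline and week-12 cIMT, so any figure here is an assumption. If baseline cIMT were an adjuster, 34 per group would give about 85 % power at a correlation of 0.3 and 91 % at 0.5. An unadjusted change score would give about 67 % and 81 %. The 81 % must therefore be read as power under the inputs of the Sample size section. The same condition applies to the plan's 85 %, so the contradiction remains.
- **The slip may lie in the dropout percentage.** Six is 15 % of 40 (one group) and 7.5 % of 80. That origin is conjecture, but the text does not show which figure is at fault, so the fix should leave the choice open.
- **Missing week-12 values may be handled elsewhere.** A separate analysis plan could do so. But the inflation from 74 to 80 is itself the plan's statement that dropouts do not count towards the 74.

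**Conclusion.** The statement is wrong as written. The base size of 37 per group is sound, and the error lies in the dropout step alone: 80 recruits allow for 7.5 % loss, not about 15 %. At 15 % loss, 34 per group remain. The planned t-test then has 81.2 % power for 0.07 mm (82.3 % by the normal approximation), and 85 % power is reached only for a difference of about 0.074 mm.

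The shortfall is about 3 points on a single method, or nearly 4 against the printed 85 %. It does not threaten the design, but it affects the figure by which the primary result will be judged.

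The result assumes SD 0.10 mm, an unadjusted two-sided 5 % t-test, no 12-week cIMT value from dropouts, and losses spread equally over the groups.

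**What to change.** Keep the target of 80 and change one sentence in the Sample size section, in one of two ways:

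- **Restate the power:** *With 80 participants recruited and 15 % dropout, 34 per group are expected to complete, giving 81 % power for a difference of 0.07 mm (85 % power for 0.074 mm), by two-sided t-test at the 5 % level with SD 0.10 mm.*
- **Restate the allowance:** keep 74 evaluable participants with 85 % power, and say that 80 recruits allow for up to 7.5 % dropout. This suits only if the sponsor really expects loss that low.

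Keeping both 85 % power and 15 % dropout would instead need 88 recruited (44 per group). That is not proposed here, since power stays above 80 % without it.

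The cost is one sentence and a slightly less favourable power figure or dropout allowance. Enrolment, outcome and analysis do not change.
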